#### The role of TAMs in the growth and progression of CNS tumors

1.1.1.

Low-grade gliomas (LGGs), including diffuse astrocytomas, account for approximately 10–20% of all primary brain tumors. Although they are more indolent relative to grade III (anaplastic) or grade IV tumors including glioblastomas (GBMs), over 95% of LGGs will undergo malignant transformation into a higher grade (III/IV) gliomas (HGGs) [2]. Depending on tumor location, glioma typically present with seizures, focal neurological signs, or symptoms of raised intracranial pressure and these tumors have a disproportionate impact on patients and wider society, often affecting young adults [3]. In other non-CNS cancers, TAMs are known to be pivotal in driving malignant transformation and may contribute to an LGG’s propensity for infiltration, recurrence and therapy resistance [4–7]. Currently, the appearance of focal contrast enhancement within these tumors, suggestive of loco-regional blood–brain barrier (BBB) disruption, is the most used sign of tumor progression in clinical practice. However, this lacks specificity, with the temporal relationship between histological transformation and appearance of new contrast enhancement unclear [8,9].

VS are histologically benign tumors, arising from Schwann cells lining the vestibulocochlear nerve at the cerebellopontine angle [10]. Whilst 95% occur as a unilateral, sporadic tumor, they can also occur bilaterally as part of the syndrome NF2-related Schwannomatosis (NF2-SWN) [11]. The associated morbidity of VS and their treatment (surgery or radiosurgery) makes management through surgery or radiotherapy particularly challenging [12]. *Ex vivo* VS tissue analysis studies have shown that TAMs compartmentalize within Antoni type B areas and are associated with increased tumor size and growth rate [13]. *In vivo* evidence for increased TAM-dependent inflammation with growing VS also stems from TSPO positron emission tomography (PET) studies, where inflammation in growing tumors is attributed to the abundance of TAMs [13]. Subsequent work demonstrated that TAMs are a targetable driver of the immune microenvironment and tumor growth in NF2-SWN-associated VS also [14–16].

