#### Cellular source of USPIO internalization in vivo

1.1.3.

The timing and mechanisms of USPIO trafficking into the brain and the exact cell-type specificity are yet to be fully understood. Previous *in vivo* models have demonstrated ferumoxytol localization within the lysosome of tumor CD68^+^/CD163^+^tumor macrophages, and within dilated astroglial end feet and astroglial processes in the parenchyma [30]. Data from human studies is limited to HGGs, and have shown iron deposition within CD68^+^/CD163^+^ TAMs following ferumoxytol (5 mg/kg) infusion, with significant positive correlations between delayed imaging and the number of CD68^+^/CD163^+^ iron-containing TAMs at time of tumor resection [26]. More recently, a study of 10 patients with IDH-wildtype GBMs, demonstrated that tissue samples from ferumoxytol enhancing regions contained significantly more M2 polarized macrophages than non-ferumoxytol enhancing tissue regions [28]. However, these studies are limited to high-grade tumors only, do not fully define the temporal relationship between vascular extravasation and intracellular uptake, nor assess their relative contributions to the evolving MRI signal. There is, therefore, a clear need for larger patient studies of USPIO-enhanced imaging in CNS tumors with comparative tissue datasets, to clarify the cellular source of the USPIO-enhanced MRI signal and evaluate the *in vivo* relationship between BBB disruption and USPIO extravasation.

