Our specific hypotheses include that: (1) early (<2 hours) USPIO-enhanced imaging will principally reflect vascular distribution and will correspond with other MRI-derived measures of tumor vascular density and perfusion; (2) delayed (24–48 hours) USPIO-enhanced imaging will principally reflect intracellular USPIO distribution within TAM, and will co-localize with but also extend beyond imaging (GBCA enhancement) and tissue markers of endothelial disruption; (3) that QSM-derived susceptibility estimates and T2*-based measures will provide optimal quantitative reliable measures of TAM density, iron abundance and cellular iron localization with imaged tumors; (4) susceptibility based measures of delayed USPIO uptake (e.g., QSM, R2* mapping) will be greater in growing VS, relative to non-growing tumors, and will reflect an increased abundance of TAM in these tumors; and (5) that regions of higher grade transformation within imaged glioma will show changes on delayed USPIO-enhanced acquisitions, in particular susceptibility-based measures such as QSM, and these regions will show greater TAM abundance on matched tissue sections compared to non-enhancing tumor regions.

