### Tissue collection

2.4.

Written informed consent is obtained from all participants for the collection and analysis of tumor tissue, with both formalin-fixed paraffin-embedded (FFPE) and fresh-frozen specimens collected at surgery. Immunohistochemistry and immunofluorescence analyses are performed on FFPE and fresh-frozen tissue to characterize USPIO uptake across immune and nonimmune cell populations. For extra-axial tumors such as VS, tumors are often completely resected allowing comparison of ferumoxytol imaging datasets with tissue across the entire tumor volume. For intra-axial tumors such as glioma, image-guided tissue sampling of non-enhancing and enhancing regions on delayed phase (>24 hours) post ferumoxytol imaging can be performed using neuronavigation software.

The interval between the final ferumoxytol MRI scan and tissue acquisition will be recorded. Surgery will be scheduled as close as clinically feasible to the final imaging timepoint, determined by clinical urgency, theater availability and standard care pathways. In line with the usual clinical pathway at our institution, for participants with glioma, it is expected, that surgery will be performed within 24 hours of the final MRI scan. For participants with VS, it is expected that surgery will be performed within 4 weeks of the final MRI scan. Acquired imaging from each timepoint (post GBCA and post ferumoxytol) will be fused using neuronavigation software. For participants with glioma, sampling will target regions within the tumor, where safe and appropriate to do so, corresponding to delayed ferumoxytol related changes, contrast enhancement and non-enhancing tumor. For participants with VS, complete or near-complete resection is standard practice at our institution but we will also use neuronavigation to allow for tissue sampling of different regions within the tumor. Sample location will be recorded for later comparison with MRI-derived maps. Imaging–histology registration will be interpreted with recognition of unavoidable spatial uncertainty arising from brain shift, tissue deformation, sampling limitations, fixation and sectioning effects, and differences between *in vivo* MRI resolution and *ex vivo* histological resolution.

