### Sample size and tumor groups

2.7.

The planned number of participants is 39 (12 sporadic VS, 12 NF2-VS patients, 15 glioma patients). This sample size reflects feasibility and the expected recruitment capacity of a single-center pilot study requiring serial advanced MRI over three days, ferumoxytol infusion, and, in surgical participants, tissue acquisition for imaging-histology comparison. Although glioma and VS are biologically distinct, both are characterized by macrophage-rich inflammatory tumor microenvironments that are implicated in tumor growth, progression and treatment response. The inclusion of both intra-axial gliomas and extra-axial VS permits assessment of our hypotheses across two clinically important CNS tumor settings with differing characteristics.

This pilot study will allow the evaluation of recruitment feasibility, scan completion rates, tolerability, missing data rates, USPIO-sensitive MRI metrics, and preliminary effect sizes for imaging-histology associations. Subgroup analyses by tumor type, VS growth status and glioma transformation status will therefore be interpreted as exploratory, to inform future larger-scale studies.

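### Hypothesis 5 compares transformed glioma with non-enhancing tumor, while its secondary endpoint compares transformed with histologically non-transformed tissue

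*Protocol article*

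**What the plan says.** All references are to the protocol article.

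- **1.2 Objectives, secondary endpoints.** One endpoint is the difference in USPIO-related signal and immune cell density between glioma regions that histology confirms as transformed and those it does not.
- **1.2 Objectives, hypothesis 5.** Regions of higher-grade transformation should change on delayed USPIO acquisitions, and "these regions will show greater TAM abundance on matched tissue sections compared to non-enhancing tumor regions". The signal part names no comparator. The TAM part does, and it is an imaging category.
- **2.4 Tissue collection.** One sentence says that "image-guided tissue sampling of non-enhancing and enhancing regions on delayed phase (>24 hours) post ferumoxytol imaging can be performed". A later one says glioma sampling will target regions "corresponding to delayed ferumoxytol related changes, contrast enhancement and non-enhancing tumor", subject to safety. Images from both contrast agents are fused and sample locations are recorded.
- **1.1.1.** Of contrast enhancement as the usual sign of progression: "this lacks specificity, with the temporal relationship between histological transformation and appearance of new contrast enhancement unclear".
- **1.1.3.** In a cited study of 10 patients with IDH-wildtype glioblastoma, ferumoxytol-enhancing samples "contained significantly more M2 polarized macrophages than non-ferumoxytol enhancing tissue regions".
- **2.7 Sample size.** Glioma patients make up 15 of the 39 planned participants. "Subgroup analyses by tumor type, VS growth status and glioma transformation status will therefore be interpreted as exploratory".

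**The concern.** Hypothesis 5 should be the prediction that goes with the secondary endpoint, but the two differ in their reference group. Under the hypothesis, a transformed region that does not enhance belongs to both sides of the comparison. An enhancing region that has not transformed belongs to neither. The article's own rationale is that enhancement and transformation do not coincide, so these are the cases of most interest.

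At stake is what a positive result would mean. If TAM density follows enhancement, transformed tissue (some of it enhancing) will show more TAM than a reference group chosen for not enhancing, whether or not transformation matters. A result of that kind could be carried into a larger study as a transformation signal.

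A second, smaller issue is sampling. The three glioma targets overlap, and tissue that is positive for both agents together with tissue negative for both would satisfy all of them. Tissue evidence on what ferumoxytol shows beyond gadolinium would then be limited.

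**Working it through.** The article gives no effect size, SD, power or error rate for this comparison, so there is no stated figure to reproduce. The check is a comparison of the texts, followed by an illustration of the mechanism.

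**1. The two contrasts.**

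| Sample | Endpoint contrast | Hypothesis 5 contrast (TAM part) |
|---|---|---|
| Transformed, enhancing | transformed | transformed |
| Transformed, non-enhancing | transformed | transformed and comparator |
| Non-transformed, enhancing | comparator | neither |
| Non-transformed, non-enhancing | comparator | comparator |

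The contrasts differ in the two middle rows.

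**2. Which agent.** The first sampling sentence in 2.4 uses enhancing and non-enhancing for delayed ferumoxytol. The later list sets non-enhancing tumor beside contrast enhancement, which suggests gadolinium. Hypothesis 5 does not settle it.
- If gadolinium is meant, 1.1.1 itself says enhancement is non-specific, so its absence is a poor stand-in for untransformed tissue.
- If delayed ferumoxytol is meant, the comparator is chosen on the marker that hypothesis 2 expects to reflect TAM. Low TAM in the comparator would then be partly built in.

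**3. Size of the effect (illustration).** Assumptions, none from the documents except the 15 patients:
- the true effect of transformation on TAM density is zero;
- enhancing tissue has TAM density higher by d SD;
- pT and pN are the shares of transformed and non-transformed samples that enhance;
- each patient gives one sample per category;
- within-patient correlation is 0.3;
- paired t-test, two-sided 0.05, 20,000 runs.

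Expected TAM difference:
- hypothesis 5, transformed minus non-enhancing: d × pT − 0 = d × pT;
- endpoint, transformed minus non-transformed: d × pT − d × pN = d × (pT − pN);
- transformed minus non-transformed within one enhancement stratum: 0.

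With d = 1, pT = 0.7 and pN = 0.3:

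| Contrast | Expected difference (SD) | Runs with p<0.05 | Range over the settings tried |
|---|---|---|---|
| Hypothesis 5 | 1 × 0.7 = 0.70 | 51% | 12–96% |
| Endpoint | 1 × (0.7 − 0.3) = 0.40 | 19% | 7–76% |
| Within stratum | 0 | 5% | about 5% |

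The settings tried were d from 0.5 to 1.5, pT from 0.5 to 0.9 and pN from 0.2 to 0.5. The last row assumes that all 15 patients supply both kinds of sample in the same stratum, which is optimistic.

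So the hypothesis 5 contrast shows a difference whenever enhancing tissue holds more TAM and some transformed tissue enhances. Moving to the endpoint comparator shrinks that difference but removes it only if pT = pN.

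**The case against.** The strongest reply is that the right contrast is already in the plan. The secondary endpoint states it, 2.7 names transformation status as the subgroup, and no analysis in 2.8 or 2.9 is written as transformed versus non-enhancing. The mismatch may be loose wording. The analysis is declared exploratory, and the primary endpoint (delayed susceptibility change against TAM density) does not use this contrast. All of this stands and limits the weight of the point. It does not settle which of the two statements governs.

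A reader might infer more: that sampling makes ferumoxytol and gadolinium status perfectly collinear, so that the tissue data hold no information on ferumoxytol beyond gadolinium and hypotheses 2 and 5 cannot be answered. The documents do not support this.
- Perfect collinearity follows only if every sample is concordant. Nothing in 2.4 says so; it lists the targets separately and gives no number of samples per patient.
- Locations are recorded and the images fused, so each sample can be classified later by histology and by both agents.
- Whether delayed uptake extends beyond gadolinium enhancement can be examined on the images, through the overlap measures in 2.9 and the voxel-wise and regional analyses in 2.8.

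It is also fair to say that samples must be chosen by imaging, since grade is unknown at surgery, and that an article may leave a detailed sampling scheme to the full protocol. What remains is narrower: the targets as printed can be met with concordant tissue alone, and later classification cannot supply discordant tissue that was never taken.

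**Conclusion.** The point holds as an internal mismatch with a real consequence for interpretation. Hypothesis 5 and its secondary endpoint use different comparators, the one in hypothesis 5 is undefined as to agent, and on either reading it lets a TAM difference tied to enhancement look like a transformation effect. The direction rests on enhancing tissue holding more TAM. The glioblastoma study cited in 1.1.3 makes that plausible for ferumoxytol enhancement; for gadolinium enhancement it is an assumption. The percentages above show the mechanism under assumed inputs and are not estimates for this study.

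The weight is moderate. The glioma transformation analysis, in 15 patients, is affected. The definition of the primary endpoint and the imaging part of hypothesis 2 are not. The sampling issue is a risk of limited tissue evidence, not a demonstrated failure to separate the two agents.

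**What to change.** 1. In 1.2, reword the TAM part of hypothesis 5 to compare histologically transformed with histologically non-transformed samples, within patient.
2. State whether gadolinium or delayed ferumoxytol defines non-enhancing, and use the term that way throughout 1.2 and 2.4.
3. Classify every glioma sample by histology, gadolinium enhancement and delayed ferumoxytol change, using the recorded locations.
4. Report the comparison stratified by or adjusted for gadolinium enhancement. Step 1 alone leaves d × (pT − pN).
5. In 2.4, under the existing safety condition and with no added samples, say that where a ferumoxytol-positive, gadolinium-negative region exists it is a preferred target alongside a region negative for both.

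The cost is wording, a classification of samples from data already recorded, and an order of preference among existing targets. There are downsides: somewhat fewer samples from the enhancing core, sparse strata with 15 patients, and discordant regions that will not exist in every patient. The stratified result will be descriptive, which fits its exploratory status.

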### Trial design

1.3.

Single-center, prospective, observational imaging pilot study

## Methods

2.

### Study setting

2.1.

Single-center study being undertaken at the Greater Manchester Neurosciences Center.

### Eligibility criteria

2.2.

Two main tumor groups of participants will be recruited for this study.

Group A: Patients with either sporadic or NF2-SWN-associated VS. The sample will include growing tumors that are being considered for surgical resection (sporadic tumors) or treatment with the anti-angiogenic agent bevacizumab (NF2-SWN-associated VS), and non-growing/static tumors that are being considered for either further radiological surveillance or surgery.

Group B: Patients with a suspected transforming LGG. Patients in this cohort will have a suspected diagnosis of an LGG on conventional clinical imaging, with or without radiological features suggestive of malignant transformation toward either grade III (anaplastic) or grade IV gliomas. Patients who are listed to undergo surgical debulking or biopsy will be enrolled into the study so that acquired imaging can be compared with tissue datasets.

*Inclusion criteria*:
Be at least 16 years oldHave a CNS tumor suspected to be one of the defined histological typesBe able to lie still for up to 1 hour comfortably

*Exclusion criteria*:
Life expectancy of <1 yearPrevious CNS radiotherapy/stereotactic radiosurgery (SRS)Pregnancy/ breastfeeding in femalesAn eGFR of <30 ml/minA documented history of iron overload/hemosiderosis/hemochromatosisPresence of other immune or inflammatory conditions e.g., rheumatoid arthritisAbsolute (e.g., pacemaker) or relative (severe anxiety or claustrophobia) contraindications to MRI scanningA history of allergic reaction to iron or dextranA history of allergic reaction to gadolinium contrast agents, asthma or renal problemsInability to understand verbal explanations or written information given in English.

### Interventions

2.3.

#### Imaging protocol

2.3.1.

Patients are recruited via specialist multi-disciplinary team meetings at the Greater Manchester Neurosciences Center. Recruited patients are then scanned at four timepoints over three days. A flowchart of participant activities is shown in Figure 2.

**Figure 2. f0002:**
[figure not shown]
Study design and scanning workflow.

On the first visit, patients undergo a baseline advanced MRI protocol at 3T, including: structural T_1_W and T_2_ FLAIR imaging (glioma only), baseline T_1_ relaxivity (R_1_) mapping (measured using a variable flip angle acquisition), SWI, T_2_ and T_2_* mapping, QSM, and DTI. Amide proton transfer (APT) imaging, a chemical exchange saturation transfer MRI technique that is sensitive to changes in proteins and peptides containing amide groups in tissue, is also performed for recruited glioma patients. It is not performed for participants with VS, as its application in the inferior brain and skull base is often limited by artifacts arising from B_0_ field inhomogeneities at air–tissue interfaces, particularly near the paranasal sinuses and external auditory canals [31]. For measuring tumor perfusion and tumor microvascular characteristics (including endothelial permeability) a multi-delay ASL acquisition and a dual-injection, dual–temporal resolution DCE-MRI acquisition is also collected. During the DCE-MRI protocol, administration of a GBCA (gadoterate meglumine; Dotarem®, Guerbet S.A.; dose of 0.2 mmol/kg) is performed, and is followed by post-contrast T1W imaging and repetition of the pre-contrast T_1_, T_2_ and T_2_* mapping, SWI, and QSM protocols. An overview of included sequences and acquisition parameters are provided in Supplementary Table S1.

After the initial baseline MRI scan, patients receive ferumoxytol at a dose of 5 mg/kg (up to maximum dose of 510 mg) as a slow intravenous infusion over 30 minutes. Patient observations (blood pressure, heart rate, temperature) are performed regularly during the infusion and up to 30 minutes afterward, due to a small risk of serious hypersensitivity reactions following IV iron infusions.

Scan 2 is performed within two hours of the ferumoxytol infusion, and incorporates the same T_1_W imaging, T_1_ relaxivity (R_1_) mapping, SWI, T_2_ and T_2_* mapping and QSM protocol used for the baseline scan. This short (<20 minutes) imaging protocol allows for the evaluation of ferumoxytol-related alterations in brain and tumor vasculature at this early timepoint. Visits 2 and 3 (scans 3 and 4) occur 24 and 48 hours, capturing the expected peak of USPIO uptake in TAMs post-infusion. During these subsequent visits, patients undergo the same brief MRI protocol as conducted at scan 2. This will enable the assessment of delayed (>24 hours) ferumoxytol-related imaging changes relative to baseline.

Since participants receive both GBCA and ferumoxytol, potential interactions between contrast-agent effects will be considered during image interpretation. Prior protocol optimization phantom experiments performed by our group, which demonstrated how GBCA is expected to predominantly influence T_1_-weighted and R_1_ measurements, whereas ferumoxytol is expected to exert stronger effects on T_2_, T_2_*/R_2_/R_2_*, SWI and QSM-derived susceptibility measures (unpublished). Accordingly, GBCA-enhanced imaging will primarily be used to define conventional enhancement and permeability-related tumor regions, while delayed ferumoxytol assessment will prioritize T_2_, T_2_*/R_2_/R_2_*/SWI and QSM-derived measures. The acquisition of R_1_, R_2_, R_2_*, T_2_*, T_2_, SWI and QSM data across pre-contrast, post-GBCA, early post-ferumoxytol and delayed post-ferumoxytol timepoints will also allow the *in vivo* signal effects of each contrast agent to be assessed across complementary quantitative imaging markers.

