### Objectives

1.2.

In this pilot study, we investigate the candidate USPIO agent ferumoxytol as a noninvasive imaging marker of TAM-driven inflammation in suspected transforming LGGs and VS. We hypothesize that delayed ferumoxytol-sensitive MRI signals reflect the transition from vascular circulation to extravascular and TAM-associated USPIO uptake within the tumor microenvironment.

The primary endpoint is to assess the association between delayed ferumoxytol-induced MRI susceptibility changes and histologically quantified TAM density, across CNS tumor subtypes with differing vascular and microenvironmental characteristics. Within this, the specific secondary endpoints are to:
Characterize the volume, pattern, and intensity of early and delayed USPIO-enhanced MRI signal in gliomas and VS and define the optimal qualitative (e.g., susceptibility-weighted imaging, SWI) and quantitative methods (e.g., quantitative susceptibility mapping, QSM and T2* mapping) for assessing delayed USPIO cellular internalization.Examine the relationship between GBCA enhancement patterns and the extent, spatial distribution and signal intensity of early (<2 hours) and delayed (24–48 hours) USPIO uptake in both glioma and VS cohorts.Examine the association between delayed USPIO-enhanced MRI signal, tissue markers of TAM abundance and VS clinical behavior, such as size and VS growth status.Evaluate QSM-derived susceptibility values as a quantitative imaging marker for detecting USPIO cellular internalization in CNS tumors, and the relationship with tissue measures of iron abundance and localization.Assess differences in USPIO-related signal changes and immune cell density between histologically confirmed transformed and non-transformed glioma regionsEvaluate the phenotype and spatial distribution of TAMs in each tumor and their relationship to USPIO uptake

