Dual-injection dual-temporal-resolution DCE-MRI data will be analyzed using the LEGATOS method [34] to derive high-spatial-resolution maps of the following key microvascular parameters: volume transfer constant (*K*^*trans*^), plasma volume fraction (_*Vp*_) and extravascular extracellular volume fraction (_*Ve*_). SWI data acquired at each timepoint will be analyzed using the ‘Segregation and Extravascular Localization of Ferumoxytol Imaging’ (SELFI) formula, which aims to characterize USPIO nanoparticle intra/extravascular compartmentalization [27]. SWI magnitude images acquired at pre-contrast, early post-ferumoxytol, and delayed post-ferumoxytol time points will be co-registered to non-contrast-enhanced T_1_-weighted images. Voxel-wise logarithmic signal intensity ratios will be calculated between pre-contrast and ‘early’ SWI maps or delayed post-contrast images to estimate relative USPIO concentrations. Subtraction of delayed from early ratio maps will yield positive SELFI^+^ and negative SELFI^–^ values. SELFI^+^ values are thought to reflect extravascular USPIO uptake localized to phagocytic cells (TAMs), whereas SELFI^–^ values indicate persistent intravascular USPIO signal, consistent with regions of higher microvascular density [27]. SELFI values will be compared with maps of quantitative relaxometry values (T_2_*, T_2_) generated using existing pipelines and QSM-derived susceptibility maps. As the SELFI method is an investigational approach and not yet an established clinical biomarker, it may be influenced by image registration error, susceptibility artifact, baseline hemorrhage or calcification, residual intravascular USPIO, and nonlinear signal behavior on SWI magnitude images. SELFI maps will therefore be interpreted alongside QSM, T_2_*, SWI and tissue-based measures rather than as a stand-alone marker of cellular USPIO uptake.

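### The early ferumoxytol scan follows a gadolinium dose on the same visit, and the plan has no rule to separate residual gadolinium from early USPIO signal in T1W, R1 and SELFI

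*Protocol article*

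**What the plan says.** **Order of agents (section 2.3.1).** GBCA is given during the baseline DCE-MRI: "dose of 0.2 mmol/kg) is performed, and is followed by post-contrast T1W imaging and repetition of the pre-contrast" T1, T2, T2*, SWI and QSM acquisitions. Ferumoxytol comes only once that scan has ended; its administration is described "as a slow intravenous infusion over 30 minutes". Scan 2 belongs to the same visit, because visits 2 and 3 are scans 3 and 4. "Scan 2 is performed within two hours of the ferumoxytol infusion, and incorporates the same" T1W, R1, SWI, T2, T2* and QSM acquisitions as baseline.

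**What the protocol says about interaction (section 2.3.1).** It recognises that the two agents may interact and leaves this to image interpretation. It cites unpublished phantom work under which "GBCA is expected to predominantly influence" T1W and R1, with ferumoxytol acting more strongly on the other metrics. The resulting preference for T2, T2*, SWI and QSM is stated for delayed ferumoxytol assessment.

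**SELFI (section 2.5.1).** "Voxel-wise logarithmic signal intensity ratios will be calculated between pre-contrast and" early, or delayed, SWI. The ratios are read as relative USPIO concentration, and the delayed map is subtracted from the early one. The listed SELFI limitations do not include residual gadolinium.

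**Where early signal is used.** Section 2.9 follows R1 over time together with T2, T2* and QSM. The second secondary endpoint in section 1.2 is to "Examine the relationship between GBCA enhancement patterns and the extent, spatial distribution and signal intensity of early" and delayed USPIO uptake.

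**The concern.** The early scan is meant to show ferumoxytol while it is still mainly intravascular. If gadolinium from the same visit is still present, part of what is measured at scan 2 belongs to the other agent. Three uses are exposed:

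- **The GBCA-versus-early comparison.** Residual gadolinium tends to lie in the voxels that enhanced with GBCA. On T1W and R1 one side of the comparison would then contain some of the other, and agreement would be partly built in.
- **SELFI.** Positive values are read as uptake in phagocytic cells and negative values as persisting intravascular agent. An error in the early term carries into that reading.
- **Temporal models of R1.** The step from baseline to scan 2 would be a joint effect of two agents, read as one.

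The protocol's safeguard covers the delayed scans, where little gadolinium should remain, and not the early scan, where it matters.

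**Working it through.** The plan states no figure to reproduce here. The check follows the timing and the stated computations.

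**1. Interval from GBCA to scan 2.** From section 2.3.1: a 30-minute infusion starts after the baseline scan is complete, and scan 2 follows within 2 h of it. The upper end is 0.5 h + 2 h = 2.5 h, plus the post-GBCA mapping and changeover (assumed about 0.5 h), so about 3 h. For the lower end, the post-GBCA mapping and the full infusion must both finish first. About 1 h is assumed.

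**2. Plasma gadolinium remaining.** The article gives no half-life. Assume 1.5–2 h and one-compartment decay, fraction = 0.5^(t / half-life):

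| Time after GBCA | Half-life 1.5 h | Half-life 2 h |
|---|---|---|
| 1 h | 0.63 | 0.71 |
| 2.5 h | 0.32 | 0.42 |
| 3 h | 0.25 | 0.35 |
| 24 h | 0.5^16 ≈ 0.00002 | 0.5^12 ≈ 0.0002 |

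The range at scan 2 is 25–71%. With a 1 h half-life it is 13–50%. With 4 h, a slower-clearance case, it is 60–84%, and 1.6% remains at 24 h. Carry-over is thus plausible at scan 2 and negligible at scans 3 and 4. These are plasma fractions. The article offers nothing to convert them into a change in R1, SWI, R2* or QSM.

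**3. Does the SELFI subtraction remove it?** Take the plain log ratios that section 2.5.1 describes, with S for SWI magnitude:

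log(S_early / S_pre) − log(S_delayed / S_pre) = log(S_early / S_delayed).

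The shared pre-contrast term cancels. A gadolinium contribution to S_early does not, because S_delayed has almost none. If only the early ratio is referred to the post-GBCA image, the result becomes

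log(S_early / S_delayed) − log(S_postGBCA / S_pre),

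which removes the gadolinium effect measured at the end of scan 1. Switching the reference in both ratios would change nothing in the difference.

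**4. Built-in agreement with GBCA enhancement.** Suppose early signal = USPIO part + residual gadolinium part, the USPIO part is independent of GBCA enhancement, the gadolinium part is proportional to it, and g is the SD of the gadolinium part divided by that of the USPIO part. The correlation with GBCA enhancement is then g / √(1 + g²):

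| g | Correlation with no true association |
|---|---|
| 0.1 | 0.10 |
| 0.25 | 0.24 |
| 0.5 | 0.45 |
| 1.0 | 0.71 |

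The documents give g for no metric, so this shows the mechanism only. It applies most clearly to T1W and R1.

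**5. Reference image by metric.** For the early SWI ratio in SELFI it is pre-contrast, explicitly. For early R1, T2, T2* and QSM none is named. Section 2.3.1 speaks only of change from baseline, for delayed scans, and scan 1 holds both pre- and post-GBCA maps.

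**The case against.** The strongest reply is that the protocol already recognises the interaction and acquires what is needed to study it. All the mapping sequences are repeated after GBCA, and section 2.3.1 says that data from the four contrast states will let the effect of each agent be assessed. How those maps enter a model may belong in a fuller document. This stands as far as it goes, but acquiring the maps corrects nothing by itself, and for SELFI the article does fix a reference, which is pre-contrast.

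Other points narrow the concern and stand:

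- Section 2.8 leaves R1 out of its list of ferumoxytol-sensitive markers, and that list is not limited to delayed scans.
- The overlap measures in section 2.9 (Dice, Jaccard, SSIM) compare post-GBCA with delayed images only. The early comparison appears as a secondary endpoint in section 1.2 without its own specified analysis.
- SELFI is described as investigational and is to be read alongside other measures.

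A reader might infer that every early metric is referred to pre-gadolinium images. The text supports this only for SELFI. A reader might also infer that early signal is biased upward throughout. That is reasonable for T1W and R1. On SWI magnitude, T1 shortening by gadolinium can raise signal and oppose the loss caused by ferumoxytol, so the early SELFI term could move either way.

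**Conclusion.** The concern holds for the early scan. As written, residual gadolinium at scan 2 would be attributed to ferumoxytol in the early SELFI ratio. Early T1W and R1 change would be a mixture of the two agents, giving some built-in agreement with GBCA enhancement under the second secondary endpoint. The distortion of SELFI has no settled sign, and subtracting the delayed ratio does not cancel it.

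The size cannot be had from the documents. The 25–71% of plasma gadolinium remaining rests on an assumed half-life of 1.5–2 h and an assumed interval of about 1–3 h, and it is not an estimate of signal bias.

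It would be wrong to conclude that the main result is compromised. The primary endpoint relates delayed susceptibility change to TAM density, and by 24 h the residue is negligible under these assumptions. It could be touched only through measures that also use the early scan, such as SELFI. The point should be settled before analysis, but it is not fatal to the study.

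**What to change.** 1. Extend the section 2.3.1 preference for T2, T2*, SWI and QSM to scan 2. Do not use early T1W or R1 as evidence of USPIO in the GBCA-versus-early comparison. In the temporal models, label the early R1 time point as a combined gadolinium-plus-ferumoxytol effect.
2. Name the reference image for each early metric. Compute early change, including the early SELFI ratio, against both the pre-contrast and the post-GBCA images, and report the two as a sensitivity range. In SELFI keep the delayed ratio on pre-contrast, since changing both references leaves the difference as it was. State that gadolinium washes out between the post-GBCA maps and scan 2. The post-GBCA reference can therefore over-correct, neither reference is exact, and the pair is not a guaranteed bound.
3. Record and report the interval from GBCA to scan 2 for each participant.

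The cost is analysis wording and one recorded time, because the images are already planned. The downside is two early estimates to report and no stand-alone claim about USPIO from early R1.
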